#### Other parameters

Sedation scoring of patients (see Table 2 for the Observer’s Assessment of Alertness/Sedation Scale (OAA/S)), duration of hospitalization, year, gender, ASA physical status of patients, dosage of intravenous and inhaling sedative drug/analgesia drug/NMBAs, duration of surgery, and anesthesia.

**Table 2 Tab2:** The Observer’s Assessment of Alertness/Sedation Scale (OAA/S) [40]

Score	Responsiveness
**5**	Awake and responds to name, spoken in a normal tone
**4**	Lethargic response to name, spoken in a normal tone
**3**	Responds only after the name is called loudly and/or repeatedly
**2**	Responds only after the name is called loudly and after mild shaking of the body
**1**	No response after the name is called loudly with mild shaking

### Statistics

#### Data management and monitoring

Data will be collected using a CRF, and all data from the CRFs will be checked by two investigators before being transferred into an Excel workbook. The digital ultrasound image/video will be copied from the ultrasound machine and stored in a mobile hard disk for review. All data will be kept by the PI independently during and after the trial. An independent Data and Safety Monitoring Committee will oversee the study conduct, report the adverse events, review the quality of collected data, and analyze the fidelity of the study to the protocol on a semiannual basis. The committee consists of a surgeon, an ICU physician, and an anesthesiologist not involved in the study. Also, the Ethics Committee of Peking Union Medical College Hospital will play a role in it. For patients who discontinue or deviate from the protocol, the data of whom will be discarded and that of a new legitimate patient will be recorded for substitution.

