### Randomization, allocation, and concealment

Once informed consent has been received and the preoperative assessment completed by major anesthetists the day before surgery, patients will be entered into the trial. The randomization procedure will be website-based using random blocks and stratified by the reversal drug the subject takes, which will be done by an independent anesthetist other than major anesthetists. That is, subjects will be randomly allocated to either the sugammadex (SUG) group or the neostigmine (NEO) group in a variable block randomization method, ensuring a 1:1 equal distribution of patients into each group. For allocation concealment, table assignment to the SUG group or the NEO group and drug preparation will be managed by a pharmacist with limited involvement in major anesthesia procedures. Besides, diaphragm ultrasound and LUS will be performed by a skilled sonographer (an independent anesthesiologist) not involved in patient care. Lastly, patients and major anesthetists are both blinded to the treatment assignment.

The randomization codes shall be sealed in duplicate and kept in envelopes by the project leader (PI). Both unblinding is performed by PI who preserved randomization codes. After the data has been blinded and determined to be reliable, the first unblinding will be carried out, only listing the group to which each patient belongs (group A or B). The second unblinding will be performed after the end of the statistical analysis, determining the SUG or NEO group. In this double-blind study, an emergency letter will be attached to every randomization code, illustrating the group and medication of the subject. Emergency letters shall be sealed and kept by PI, and shall not be opened unless there is an emergency and it is necessary to know the medication he/she has received. Once opened, the trial of this patient will be discontinued, and the reason shall be documented in the case report form (CRF).

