#### Sample size calculation

There have been no large-scale studies to confirm the actual incidence of PPCs in patients over 60 years undertaking arthroplasty. Referring to previous literature, the incidence of PPCs is15.4%, 19.2%, and 48.3% in the elderly [18, 26, 41]. To make the results of our study more reliable, we use 15.4% for sample size calculation. The overall incidence is around 5% in all patients undertaking non-cardiac surgery with general anesthesia and endotracheal intubation [15]. The necessary sample size has been calculated using the statistical software PASS 15. The analysis shows that at least 207 patients per group will be necessary (with a 95% confidence interval (CI), a power of 90%, 20% loss of follow-up), that is, 414 patients in total.

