#### Statistical analyses

All statistical analyses will be performed by a statistician blinded to the group allocation. Percentages will be calculated for dichotomous data and analyzed by the *χ*^2^ test. Continuous variables will be expressed as mean ± standard deviation and median (ranging from 25th to 75th percentiles) and analyzed with the *T*-test and Mann-Whitney rank sum test. The paired sample *t*-test is used for comparison of the same index. Spearman and Pearson correlation analyses are used for the correlation analysis of normal distribution variables and non-normal distribution variables, respectively. *P* < 0.05 is considered statistically significant. IBM SPSS Statistics 25 is used as our statistical software. Multiple imputation will be used for handling missing data.

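### Discarding and replacing every randomised patient who discontinues or deviates, emergency-unblinded patients included, compromises the as-randomised comparison of PPCs to day 30

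*Protocol article*

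**What the plan says.** The rule stands in the protocol article under Data management and monitoring. It applies to anyone who stops the trial early or departs from the plan: "the data of whom will be discarded and that of a new legitimate patient will be recorded for substitution". It does not limit when the deviation occurs, how serious it is, why the patient stopped, or whether a pulmonary complication has already been recorded. It does not say to which arm the substitute is assigned.

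Under Randomization, allocation, and concealment, the article says of the sealed emergency letter: "Once opened, the trial of this patient will be discontinued, and the reason shall be documented in the case report form (CRF". An emergency-unblinded patient is therefore a discontinued patient, and the discard rule applies.

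Two other provisions deal with incomplete patients. Under Statistical analyses: "Multiple imputation will be used for handling missing data". Under Sample size calculation, the number is set with "a power of 90%, 20% loss of follow-up". The article nowhere states that patients are analysed in the group to which they were randomised.

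**The concern.** The trial is presented as a randomised superiority trial, and its primary outcome is the incidence of postoperative pulmonary complications (PPCs) to day 30, with percentages compared by a chi-square test. That test compares like with like only if group membership is fixed at randomisation. Here, membership of the analysed set depends on what happens afterwards.

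The link to the outcome is plausible from the protocol's own content. A letter is opened only in an emergency in which the medication must be known. Respiratory failure and bronchospasm are conceivable emergencies of that kind, and both count as PPCs in Table 1. Such a patient would have the primary event and then be removed, and a patient without that history would take the place. If this happens more often in one arm, the difference between arms is distorted. It could favour either drug, depending on which arm loses more events.

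There is also a question of which rule governs. A patient who leaves before day 30 could be discarded and replaced, imputed, or counted against the 20% loss allowance, and the article does not say where one provision ends and the next begins.

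**Working it through.** **1. The plan's own figure.** Inputs from Sample size calculation: 15.4%, 90% power, 20% loss, 207 per group. Assumed: 5% is the sugammadex rate (the article quotes 5% but does not assign it to that arm), and the test is two-sided at 0.05. Unpooled formula:

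n = (1.960 + 1.282)² × (0.154×0.846 + 0.05×0.95) / (0.154 − 0.05)² = 10.507 × 0.17778 / 0.010816 = 172.7, so 173 per group.

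173 × 1.2 = 207.6, which matches 207. The figure reproduces, so this point does not rest on a sample-size error.

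**2. Effect of discarding on the observed rate.** Let p be the true PPC rate, d_e the share of patients with a PPC who are discarded, and d_n the share of patients without one. After discarding and replacing, with substitutes subject to the same rule, the expected observed rate is

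p(1 − d_e) / [p(1 − d_e) + (1 − p)(1 − d_n)].

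The article gives no discard rates, so d_e and d_n are assumptions. I set d_n = 5% in both arms and vary d_e. Replacement is assumed to hold each arm at 207.

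Example, no true difference (15.4% in both arms), 30% of neostigmine (NEO) events and 10% of sugammadex (SUG) events discarded:
- NEO: 0.1078 / (0.1078 + 0.8037) = 11.8%.
- SUG: 0.1386 / (0.1386 + 0.8037) = 14.7%.
- Share of all patients discarded: NEO 0.154×0.30 + 0.846×0.05 = 8.9%; SUG 0.154×0.10 + 0.846×0.05 = 5.8%.

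**3. Rejection rates.** Exact binomial enumeration, 207 per arm, uncorrected chi-square test, two-sided 0.05:

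| Events discarded, NEO / SUG | Observed rates if 15.4% in both | Type I error | Power if 15.4% vs 5% |
|---|---|---|---|
| No discarding | 15.4% / 15.4% | 4.9% | 95% |
| 30% / 30% | 11.8% / 11.8% | 4.9% | 88% |
| 10% / 5% | 14.7% / 15.4% | 5.4% | 93% |
| 20% / 10% | 13.3% / 14.7% | 6.9% | 87% |
| 30% / 10% | 11.8% / 14.7% | 13.7% | 75% |
| 5% / 30% | 15.4% / 11.8% | 18.3% | 99% |

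In the last row the high rejection rate is not a gain. The expected observed rates under 15.4% vs 5% are 15.4% and 0.035 / (0.035 + 0.9025) = 3.7%, a difference of 11.7 points against a true 10.4, so the effect is exaggerated.

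**4. A second parameterisation.** Let discards be unrelated to outcome in one arm. In the other, a share d is discarded whose PPC risk is k times 15.4%, so the observed rate there is (0.154 − d×k×0.154) / (1 − d). Normal approximation, no true difference:
- d = 5%, k = 1.5: 15.0%, rejection rate 5.2%.
- d = 10%, k = 2: 13.7%, 7.8%.
- d = 10%, k = 3: 12.0%, 17.3%.
- d = 20%, k = 2: 11.6%, 20.9%.

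Both approaches say the same: the effect is negligible when discards are few or unselective, and material when they are selective and unequal.

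**5. The three provisions side by side.** For one patient who discontinues before day 30, discard-and-replace and imputation cannot both apply, and a loss allowance is not needed for a loss that is replaced. For an adherent patient who simply cannot be reached by telephone on day 30, imputation and the allowance both still make sense. The same holds for imputing missing items in retained patients. The overlap is real but partial.

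**The case against.** The strongest reply is that nothing shows the rule would remove many events, or more in one arm than in the other. The article gives no deviation rate and no observed link between deviation and PPCs. Patients and the treating anaesthetists are blinded, which limits arm-driven discarding. Patients enter the trial the day before surgery, so some discards would precede the reversal drug and cannot be caused by it. Mild patterns barely move the error rate. All of this stands, and it limits the size of the claim. It does not rescue the rule, because blinding does not prevent deviations that the drug or the outcome itself brings about.

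A reader might go further in several ways that the article does not support:
- *The data are lost for good.* The Data Availability section says that all compiled case report forms will be archived, and the project leader keeps all data. Exclusion from the analysis set is the more natural reading.
- *Slow recovery on neostigmine is a deviation.* Under the stated extubation criteria, a patient who stays intubated until the train-of-four ratio exceeds 0.9 is complying; only earlier extubation would deviate. This gives no ground for predicting more discards in that arm.
- *The rule flatly contradicts multiple imputation and the 20% allowance.* The conflict is partial, as shown above.
- *Records have already been discarded.* The article says only that recruitment is under way.

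**Conclusion.** The point holds. The rule is stated in the protocol itself, so it is not a detail left to a fuller document. As written, it removes patients after randomisation without limit, and emergency-unblinded patients are caught by a direct reading of two sections together. The as-randomised comparison is compromised. To call it destroyed would need discard rates that the article does not give.

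Under the assumed fractions, type I error lies between about 5% and 18.3%, and the direction of bias is open. Power at 15.4% vs 5% falls from 95% to 93%, 87% or 75% in the three unequal patterns that remove more neostigmine events. These figures rest on 207 analysed per arm, 5% of non-events discarded, and 5% as the sugammadex rate. Confidence is high that the rule exists and is unsound; it is low on how large the bias would be or which way it would run. The rule should be changed before analysis.

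**What to change.** Delete the discard-and-substitute sentence and state instead:
- Day-30 outcome data are collected on all randomised patients, including those who deviate and those whose emergency letter is opened. This concerns data collection only; when a letter may be opened is untouched.
- The primary analysis includes all of them in the group to which they were allocated.
- For the primary outcome, multiple imputation is used only where day-30 status is unknown. The 20% allowance covers that same loss.
- The deviation-free set is reported as a sensitivity analysis.
- Any records already excluded are brought back from the archived case report forms.

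**Cost.** A wording change, follow-up of the retained patients, and retrieval of forms if any were set aside. The total can stay at 414, but the observed effect may be diluted. If a share f of sugammadex patients deviate and gain no benefit, the sugammadex rate becomes 0.05(1 − f) + 0.154f, that is 5.52%, 6.04% or 7.08% for f = 5%, 10% or 20%. Power at 207 per arm (normal approximation; 94.1% without dilution) is then about 91%, 87% or 77%. The shares are assumptions. Holding 90% power would need about 200, 228 or 301 observed patients per arm, so the team should look at its deviation rate, still blinded, before deciding whether 414 is enough.

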#### Sample size calculation

There have been no large-scale studies to confirm the actual incidence of PPCs in patients over 60 years undertaking arthroplasty. Referring to previous literature, the incidence of PPCs is15.4%, 19.2%, and 48.3% in the elderly [18, 26, 41]. To make the results of our study more reliable, we use 15.4% for sample size calculation. The overall incidence is around 5% in all patients undertaking non-cardiac surgery with general anesthesia and endotracheal intubation [15]. The necessary sample size has been calculated using the statistical software PASS 15. The analysis shows that at least 207 patients per group will be necessary (with a 95% confidence interval (CI), a power of 90%, 20% loss of follow-up), that is, 414 patients in total.

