#### Maintenance of anesthesia

Sevoflurane will be supplied at an age-adjusted end-tidal concentration of 1.0 minimum alveolar concentration (MAC) in an air/oxygen mixture. Fentanyl will be titrated with a bolus of 0.5 μg kg^−1^ every 30 min, to keep an adequate level of analgesia. To maintain neuromuscular block, rocuronium will be re-administered when TOFc exceeds 2 with a bolus of 0.2 mg kg^−1^. Mechanical ventilation will be set at 6~8 ml/kg referred to the ideal body weight as tidal volume and 12~15 rates per minute as respiratory rates according to respiratory carbon dioxide ranging from 30 to approximately 40 mmHg. Extubation will be performed when all the following criteria are met: (1) the patient is awake and can execute simple commands, (2) the patient’s respiratory pattern is regular with a tidal volume of 6–7 ml/kg referred to ideal body weight, and (3) the TOFr is > 0.9.

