## Discussion

From the aspect of pharmacologic profile, the rationale of this comparison study is that PORC may be unavoidable with neostigmine as a reversal agent since it has a relatively short duration and ceiling effect for deep neuromuscular block, as well as some adverse cardiac effects to be concerned. Meanwhile, sugammadex was reported to be superior to reverse aminosteroid neuromuscular blockade, such as rocuronium and vencuronium than traditional anti-cholinesterase, neostigmine.

Logically, the residual effect of neuromuscular block may result in PPCs by mechanisms of ventilatory muscle weakness, impaired swallowing reflex, inability to cough, etc. PPCs are a major contributor to the overall risk of surgery and are associated with high in-hospital mortality. The STRONGER study, which is a retrospective observational matched cohort study, demonstrated that the incidence of PPCs is 30–50% lower by administrating sugammadex than neostigmine [15]. However, another randomized trial that enrolled 200 patients has shown that sugammadex can significantly lower the incidence of PORC, whereas it cannot obtain a significantly decreased rate of PPCs [24]. Such being the case, we do not have conclusive findings. The incidence of PPCs due to multiple perioperative reasons is about 5% in surgical patients [15]; thus, a large sample-sized randomized controlled trial will be necessary to reveal the truth. Our study tried to focus on relative elderly patients who are vulnerable to cardiopulmonary stress and therefore speculated the reduction of PORC by sugammadex will bring better outcomes against PPCs for such an extent population.

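### The 207 per arm reproduces only with about 5% PPCs under sugammadex, an all-patient figure; for the cited 30–50% reduction from 15.4%, power is about 24–60% (28–70% with no loss), not 90%

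*Protocol article*

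**What the plan says.** The Sample size calculation section of the Protocol article lists three incidences in elderly patients (15.4%, 19.2% and 48.3%) and settles on the lowest: "we use 15.4% for sample size calculation". It then adds a figure from reference 15: "The overall incidence is around 5% in all patients undertaking non-cardiac surgery with general anesthesia and endotracheal intubation". The conclusion is: "The analysis shows that at least 207 patients per group will be necessary". The conditions given are "with a 95% confidence interval (CI), a power of 90%, 20% loss of follow-up", for a total of 414. The section states no sugammadex rate, no effect size and no sidedness.

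The Discussion describes the 5% the same way: "The incidence of PPCs due to multiple perioperative reasons is about 5% in surgical patients". From the same reference 15, a retrospective matched cohort, it also reports that "the incidence of PPCs is 30–50% lower by administrating sugammadex than neostigmine".

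**The concern.** A two-group superiority calculation needs two event rates. The section names one as used and places a second beside it without saying which arm it belongs to. If the second is the sugammadex rate, the planned effect is the gap between elderly patients and surgical patients in general. That gap is not an estimate of what changing the reversal drug does in patients over 60. The article does print such an estimate, and it is smaller.

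The 90% would then describe an effect that nothing in the article supports. A reader who sees 90% power and a non-significant primary result would tend to conclude that sugammadex does not help. The trial could in fact have had well under 90% power for the effect its authors cite.

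**Working it through.** **Inputs.** Control rate 15.4%, power 90%, loss 20% and 207 per group (Sample size calculation); 1:1 allocation (Randomization, allocation, and concealment); superiority (Study design/setting); χ² test and significance at 0.05 (Statistical analyses). Two-sided testing is an assumption. The sugammadex rate is inferred.

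**Step 1: reproduce 207.** Try 15.4% against 5%, using the normal approximation with unpooled variance:

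n = (1.960 + 1.282)² × [0.154 × 0.846 + 0.05 × 0.95] / (0.154 − 0.05)²
= 10.507 × (0.1303 + 0.0475) / 0.010816 = 172.7 per arm; × 1.2 = 207.3.

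Exact enumeration of the uncorrected χ² test gives power 0.8986 at 165 per arm and 0.9005 at 166; 166 / 0.8 = 207.5. Two separate routes therefore lead to 207, both with 5% as the second rate.

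**Step 2: try the other printed figures.** Pooled variance, two-sided 5%, 90% power, divided by 0.8:

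| Rates compared | Enrolled per arm |
|---|---|
| 15.4% vs 19.2% | 2602 |
| 15.4% vs 48.3% | 52 |
| 19.2% vs 48.3% | 68 |
| 19.2% vs 5% | 137 |
| 48.3% vs 5% | 25 |
| 15.4% with a 30% reduction (10.8%) | 1399 |
| 15.4% with a 50% reduction (7.7%) | 452 |
| 15.4% vs 5% (same formula) | 220 |

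Only the last row is near 207, and the routes in Step 1 bring it to 207. Allowing other formulas and a 3% tolerance, second rates of about 4.2–5.7% two-sided, or up to 6.5% one-sided, also fit with 15.4%. Even 6.5% is a 58% reduction (1 − 0.065/0.154).

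**Step 3: the implied effect.** 15.4 − 5 = 10.4 points; 1 − 5/15.4 = 67.5% relative. The cited 30–50% reduction from 15.4% gives 10.8% to 7.7%.

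**Step 4: power for the cited reduction.** Exact uncorrected χ² test, two-sided 5%. 207 × 0.8 = 165.6, taken as 165 evaluable.

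| Control rate | Reduction | Power, 165 per arm | Power, 207 per arm |
|---|---|---|---|
| 15.4% | 50% | 60% | 70% |
| 15.4% | 40% | 40% | 48% |
| 15.4% | 30% | 24% | 28% |
| 19.2% | 50% | 71% | 80% |
| 19.2% | 30% | 29% | 35% |
| 48.3% | 50% | 99.6% | 99.9% |
| 48.3% | 30% | 77% | 86% |

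The pooled normal approximation agrees to within about one point (15.4%, 165 per arm: 59.1%, 39.8%, 23.7%).

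**The case against.** Several counter-arguments have weight.

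- **The 5% is never called the sugammadex rate.** True, and it should be described as an inference. The inference is strong: every second rate that fits with 15.4% implies a reduction of about 58% or more.
- **The control rate is uncertain, and the lowest one was chosen as a precaution.** This stands as a qualification. The Background ties the 48.3% to neostigmine or no reversal, and at that rate power for 30–50% is about 77–99.6% with 165 per arm. An unprinted 35% reduction from 48.3% would also land near the target (175 × 1.2 = 210). But the section says 15.4% was the rate used, so the printed power claim has to be judged from there. At 19.2% power still falls short of 90%.
- **165 evaluable may be pessimistic.** Patients who discontinue or deviate are to be replaced, and multiple imputation is planned. That is why both columns are shown; the shortfall remains at 207.
- **The 30–50% comes from a retrospective cohort in a different population.** Correct. It is the article's own benchmark, not a known effect in elderly arthroplasty patients.

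A reader might also infer four stronger points, which the article does not support:

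- **That 207 comes from multiplying by 1.2 where dividing by 0.8 was needed, so delivered power is 88%.** The exact calculation reaches 207 with the correct division and gives 90% to rounding at 165. For the same reason, a claim that 90% power needs a sugammadex rate of 4.7% (a 69% reduction) falls away.
- **That the extubation rule "3) the TOFr is > 0.9" narrows the expected difference.** No figure supports this, and the article's premise is that the diaphragm may remain weak despite an adequate ratio.
- **That the cited 200-patient randomised trial shows a smaller effect.** Its non-significant PPC result is not evidence of that.
- **That a null result is the likely outcome throughout the 30–50% range.** At a 50% reduction from 15.4% power is 60–70%, so significance is more likely than not.

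**Conclusion.** The point holds for the power claim as written. The 90% is right for a fall from 15.4% to about 5%, and the arithmetic behind 207 is sound for those rates. The article gives no basis for 5% as the rate in patients over 60 given sugammadex, and the 67.5% reduction it implies lies outside the 30–50% quoted from the same reference.

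From the chosen 15.4%, the chance of missing a true halving of PPCs is about 40% with the planned loss and 30% without it. For a 30% reduction it is about 76% and 72%. These figures assume a two-sided 5% uncorrected χ² test. They do not show what the true effect or control rate will be; they show that the 90% is conditional on an effect the article neither states nor justifies.

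**What to change.** In the Sample size calculation section:

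1. State both assumed rates and the arm each belongs to: 15.4% with neostigmine and, if confirmed as the value used, 5% with sugammadex. State the sidedness.
2. Replace the unconditional 90% with power of 90% for about a 67% relative reduction (15.4% to 5%).
3. Remove the all-patient 5% as support for the sugammadex rate. Either justify a two-thirds reduction in this population or label it as an optimistic planning assumption.
4. Print beside it the power for the reduction in reference 15: about 60% (50% reduction) and 24% (30% reduction) with 165 evaluable per arm, or 70% and 28% with 207. Add the 19.2% and 48.3% rows if the control rate is considered open.
5. Add one sentence saying that, given this power, a non-significant primary result will not be read as showing no benefit.

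The cost is a wording change, best made before unblinding since recruitment is already under way; the stated power becomes less favourable. No added enrolment is asked for. For scale only, 90% power with 20% loss would need 904 patients in total for a 50% reduction from 15.4% (452 × 2) and 2798 for a 30% reduction (1399 × 2).
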